### Treatment Protocol

An investigator's brochure will be provided to guide all clinical trial staff in protocol details.

Participants will take two capsules of active or placebo medications, orally, twice per day for 52 weeks. Medications will be dispensed at baseline and week 13, 26 and 39 visits. Participants will attend clinic visits at baseline (week 0), and at 4, 13, 26, 39 and 52 weeks for progress and/or adverse event reporting with their sites principal investigator and to collect the next stage supply of medication. Participants and investigating staff will be blinded to treatment allocation until the end of the trial when the data analyses are completed, and the coding is unlocked. Assessments conducted between weeks -2 (screening) and 0 (baseline) will become the baseline assessments for the study. During the course of the study, assessments will be conducted at weeks 2 (via phone), 4, 13, 26, 39, 52 and 65 (follow-up) weeks after the commencement of treatment (See Table 1). Follow-up assessment questionnaires (65 weeks) will be completed after the treatment period and any adverse events will be closely monitored and reported. All participants will receive 12-months trial medication at the end of the 65-week follow-up period based on compassionate grounds as the product has not yet been made available for purchase in Australia as was anticipated. Provision of the complementary medication will be subject to the principal investigator's judgement and approval by the coordinating chief investigator. Participant's general practitioner and usual specialist (if relevant) will be informed of the participant's medication prescription and safety will be closely monitored during this period via telephone calls every three months, and requesting participants to continue to keep their adverse

event diary. Participants will also be asked to undergo identical pathology tests that have been conducted throughout the trial.

Medication containers will be labelled according to the randomisation schedule at an external location and transferred to all participating centres where they will be kept in a secure storage room and maintained below 30 degrees Celsius. At each appointment, an allocation of medication will be dispensed to participants by hospital pharmacists/research personnel according to the pre-coded container labelling. Participants will be required to return the original containers and any unused medication for monitoring. Any unused medication will then be destroyed locally with approval of the coordinating chief investigator. All delivered and dispensed, unused and returned quantities will be recorded in a medication log.

### MRI Scanning Substudy

MRI scans will be performed in 50 VaD or AD + CVD participants in accordance with a standardised scanning protocol. Structural MRI, MRA and dynamic contrast enhanced (gadolinium) perfusion MRI will be performed on a GE 3 Tesla 750W wide bore scanner and 32-channel Nova head coil at Macquarie Medical Imaging (MMI) within 60 mins. Our structural scan (T1-weighted and FLAIR) protocols and diffusion scan protocols have been developed in line with the proposal from the Alzheimer's Disease Neuroimaging Initiative (ADNI). Standardised protocol: 3D T1-weighted contiguous coronal sections through whole brain (T1-TFE sequence and 3D acquisition) with voxel size 1 x 1 x 1 mm^3; 3D T2-weighted FLAIR contiguous axial slices whole brain with voxel size 1 x 1 x 1 mm^3. Then we will perform susceptibility weighted imaging (SWI) for examining cerebral microbleeds. High directional (61-gradient directions) diffusion weighted imaging (DWI) will then follow. We will then carry out angiogram (MRA) scan before taking gadolinium-perfusion scan which is for generating cerebral blood flow and volumes. We will then do a post-gadolinium enhancement volumetric T1-weighted (this has better grey/white matter contrast than the pre-gd T1-weighted). We have all these T1 and T2 volumetrics (including pre- and post-gd T1s) for an accurate estimation of brain volumetric changes in 12 months. Images will be de-identified, and then transferred to a secure workstation at Centre for Healthy Brain Ageing (CHeBA), UNSW. This protocol will remain the same for 12-months follow-up scans.

### **Study Procedures: Schedule of Assessments**

In response to the COVID-19 outbreak in Australia, study procedures have been amended to protect the safety and wellbeing of participants, their caregivers as well as the research team, and to minimise the impact of the outbreak on the SLT001 trial. Recruitment is to be paused until the trial centre's public health directive and the relevant governance body allow for recruitment to resume. All COVID-19-related strategies are detailed in Appendix 4 of this document. Once the COVID-19 outbreak ceases as per the Australian government's directive, Appendix 4 will cease to be used.

### **Screening Visit (Week -2 to 0)**

Participants eligible for study recruitment, and their study partner/carer, will have the nature, purpose, and risks of the study explained to them by the investigator. Participants (or person responsible), and their study partner/carer, agreeing to participate in the study will sign the informed consent documents. A unique subject screening number will be issued at the time of consent. The screening visit should occur within 2 weeks prior to randomisation (week 0).

Procedures will be performed in the following order:

- Informed Consent
- Medical history, prior and concurrent medications, and demographics will be documented.
- Body weight and height will be measured.
- Physical examination.
- Blood pressure, pulse rate.
- Neurological Assessment including NINCDS-AIREN diagnostic criteria, NINCDS-ADRDA diagnostic criteria, MMSE, GDS, and check of inclusion and exclusion criteria.
- Blood samples taken and sent to central laboratory for haematology, coagulation, liver function, renal function and electrolytes
- Check concomitant medications and procedures, including any planned hospital admissions.

### **Baseline visit (Week 0)**

Participants who meet all of the inclusion and none of the exclusion criteria will be scheduled to return to the site for their Baseline visit. At Baseline, the following will be performed:

- Check of inclusion and exclusion criteria.
- Check concomitant medications and procedures and note any changes in the CRF.
- Complete assessment scales VaDAS-cog, ADCS-ADL, CIBIC-plus, DEMQOL, NPI-C, CLOX and EXIT-25
- Complete MRI scans for substudy (50 participants only).

### **Week 2 Telephone contact**

- Record all AE/SAEs in the CRF

### **Week 4 Visit**

- Check concomitant medications and procedures and note any changes in the CRF.
- Vital signs (HR, BP, Ht, Wt) will be measured
- Haematology, coagulation and liver and renal function tests
- Record all AE/SAEs in the CRF
- Record compliance rates

### **Week 13 Visit**

- Check concomitant medications and procedures and note any changes in the CRF.
- Vital signs (HR, BP, Ht, Wt) will be measured
- Haematology, coagulation and liver and renal function tests
- Record all AE/SAEs in the CRF
- Record compliance rates and capture ‘success of blind’ information

### **Week 26 Visit**

- Vital signs (HR, BP, Ht, Wt) will be measured
- Haematology, coagulation and liver and renal function tests
- Record compliance rates and capture ‘success of blind’ information
- Complete assessment scales VaDAS-cog, ADCS-ADL, CIBIC-plus DEMQOL, NPI-C, CLOX and EXIT-25
- Check concomitant medications and procedures and note any changes in the CRF
- Record all AE/SAEs in the CRF

### **Week 39 Visit**

- Vital signs (HR, BP, Ht, Wt) will be measured
- Check concomitant medications and procedures and note any changes in the CRF
- Haematology, coagulation and liver and renal function tests
- Record all AE/SAEs in the CRF
- Record compliance rates and capture ‘success of blind’ information

### **Week 52 Visit**

- Vital signs (HR, BP, Ht, Wt) will be measured
- Haematology, coagulation and liver and renal function tests
- Complete assessment scales VaDAS-cog, ADCS-ADL, CIBIC-plus, DEMQOL, NPI-C, CLOX and EXIT-25
- Check concomitant medications and procedures and note any changes in the CRF
- Record all AE/SAEs in the CRF
- Record compliance rates and capture ‘success of blind’ information
- Complete MRI scans for substudy (50 participants only).

### **Week 65 Visit**

- Complete assessment scales VaDAS-cog, ADCS-ADL, CIBIC-plus

- Complete subject summary section
- Check CRF for completion and sign Investigator Declaration

## **MRI Scanning Procedures**

MRI scans will be performed in 50 VaD or AD + CVD participants in accordance with a standardised scanning protocol. Each MRI session will take 60 minutes. MRI acquisitions will be performed in the following sequential order: a) volumetric (3D) T1-weighted (7 minutes); b) volumetric T2-weighted (3 minutes); c) volumetric Fluid-attenuated inversion recovery (FLAIR) (3 minutes) and they all have a spatial resolution of  $1 \times 1 \times 1 \text{ mm}^3$ . Then the following will be carried out: d) susceptibility weighted imaging (SWI) (7 minutes), diffusion weighted imaging (DWI, 61 gradients; 15 minutes), Gadolinium contrast enhanced perfusion (Gd perfusion) (2 minutes); following this we will perform a post Gd volumetric T1-weighted scan (7 minutes).

## **Drug Accountability**

On an ongoing basis all study drugs will be reconciled against delivery, use and returned medication documents. Study drugs which are not used may be destroyed in a suitable facility locally after drug accountability has been completed and with confirmation from the coordinating chief investigator. To be compliant with the treatment protocol study, drug dosing must have a compliance rate of at least 70% over the 52-week study period. Treatment compliance will be calculated by dividing the actual number of capsules taken with expected number of capsules to be taken for the treatment period and multiplying by 100. Self-reported measures of compliance will involve asking participants and their study partner/carer to complete a diary between visits. The researchers will also ask about their adherence to the prescribed treatment regime at the week 4, 13, 26, 39 and 52 visits.

## **Data Management Protocol**

The following source data records will be utilised:

- Participant recruitment log
- Participant screening log

- Subject medication dispensing log
- Medication accountability log
- Informed consent documentation
- Clinic notes
- Expenditure records
- Participant case record forms for screening and data collection. These records will be dated and signed for correct coding, completeness, accuracy and legibility by the chief investigators.
- Adverse event report form

## 4. ETHICAL CONSIDERATIONS

### 4.1 Ethical guidelines

This research will be conducted in accordance with the International Ethical Guidelines for Biomedical Research Involving Human Subjects prepared by the Council for International Organisations of Medical Sciences (CIOMS) in collaboration with the World Health Organisation (WHO), the Australian National Statement on Ethical Conduct in Research Involving Humans and the International Conference on Harmonisation of Technical Requirements for Registration of Pharmaceuticals for Human Use and the ICH Guidelines for Good Clinical Practice (CPMP/ ICH/135/95).

Ethics approval will be sought from Human Research Ethics Committees (HREC) for all participating research institutions. The study and investigators will be accountable to these committees by way of ongoing update reports and by providing full access to source data documents.

The trial details will also be submitted to the TGA via CTN (Clinical Trial Notification) arrangements, which will include submission of notification fee and documents of ethical (HREC), sponsor, principal investigators and trial site approval.

### 4.2 Safety and tolerability of interventions

Acute toxicity tests on *SLT* were undertaken in mice. The maximum tolerated dose (MTD) for the formula as whole, ginsenosides, flavone-glycosides and crocins was 1.7 g/kg, 4 g/kg, 1.3g/kg and 5.0 g/kg, respectively, all of which are significantly higher than the proposed clinical dose

(655x, 3422x, 1109x and 20486x respectively). A long term toxicity study was also conducted in dogs. The MTD of *SLT* is 200 mg/kg, which is 70 times higher than the clinical dose. In an *in vitro* study, the inhibitory capacity of *SLT* was evaluated on 5 cytochrome P450 isoenzymes recommended by the US FDA for drug interactions studies. The median inhibitory concentration (IC50) values for CYP1A2, CYP2B6, CYP2D6, CYP2E1 and CYP3A4 were 50-140-fold higher than those potentially achievable by the therapeutic doses. This indicates that *SLT* treatment is unlikely to cause significant herb-drug interactions.

Information about adverse events will be collected by means of a standard question at each visit: “Have you had any health problems since the previous visit?” and liver and renal function and routine haematological tests will be conducted at baseline, 4, 13, 26, 39 and 52 weeks after the commencement of the treatment. In addition, participants can contact the principal investigators in the event of concerning health problems. The investigators will contact the research physicians and/or other members of the research team, who will review the dosage and continuation status in the trial, provide medical advice and/or communication with their General Practitioner or other health professionals and co-ordinate emergency medical attention as is appropriate and required. Only in the event of discontinuation in the trial will the randomisation assignment for that participant be made known. If an adverse event is present when the clinical trial is terminated, its course will be followed until the event resolves or the investigator deems it to be unrelated to the trial and appropriate case management is organised.

The definitions for adverse events are presented in Appendix 2. As with most herbal medicines, some mild adverse events might be experienced by some participants. Chinese medicine theory suggests such events may be part of the detoxification and body balancing process, although no evidence can confirm this. Examples of mild adverse events which might be encountered in this study are herbal sensitivity or intolerance symptoms of sore throat, skin rash, vomiting, nausea, asthma, headache, dry mouth, dizziness and insomnia. Moderate to major adverse events might involve impairment of liver and kidney function, abnormal clinical findings of non-physiological variance or other biochemistry abnormalities. Although serious adverse events (SAEs) are not anticipated for this trial, SAE procedures will be followed in these circumstances.

All adverse events will be recorded as part of trial records or submitted as required to Human Research Ethics Committee(s), TGA and the Department of Health. The reporting of adverse events will be consistent with TGA guidelines which are in turn based on the Note for Guidance on Good Clinical Practice (CPMP/ICH/135/95) and Note for Guidance on Clinical Safety Data

Management: Definitions and Standards for Expedited Reporting (CPMP/ICH/377/95) and according to any requirements of the Human Research Ethics Committee.

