## Safety endpoints

- Number of Adverse events and serious adverse events will be monitored during the course of the study.
- Changes in liver, renal, coagulation will be monitored during the course of the study.

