### *Inclusion Criteria*

To participate in this study, participants must be:

- 40-85 years old\*;
- Outpatients diagnosed with either probable VaD as defined by the National Institute of Neurological Disorders and Stroke (NINDS) and the Association Internationale pour la Recherche et l'Enseignement en Neurosciences (AIREN) (Roman et al, 1993) or possible Alzheimer's Disease as defined by the National Institute of Neurological and Communication Disorders and Stroke (NINCDS)-Alzheimer's Disease and Related Disorders Association (ADRDA) (McKhann et al, 2004) with significant neuroimaging (CT or MRI) evidence of cerebrovascular disease;
- An MMSE score between 10 - 24 for the diagnosis of mild to moderate dementia;
- Absence of severe depression (Geriatric Depression Scale 15-item version, total score  $\leq 11$ );
- Stable or controlled by optimal medication over a minimum of 6 months if on cholinesterase inhibitors and 3 months for (if present) hypertension, diabetes, cardiac disease or stroke, or if on hypnotics and sedatives, stabilised for more than 3 months prior to inclusion in the study;
- Agreement to take part in the study as evidenced by a personally signed and dated informed consent document indicating that the subject (or a legally acceptable representative if the subject is unable to provide consent), has been informed of all pertinent aspects of the study;
- Participants must also be accompanied by a study partner/carer, and this person must be able to assist the participant comply with the study protocol. This requires the study partner/carer to be in contact with the participant at least 2 days per week;
- If female, has no intention to become pregnant during the study.

\* *Rule waiver:* a participant aged over 85 years may still be eligible for enrolment if he/she fulfils the following two conditions:

- (1) the participant meets all inclusion and exclusion criteria of the study;

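### The visit question that elicits adverse events is worded only to a participant with dementia, and the protocol neither puts it to the mandatory study partner nor makes the diary an adverse event source

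*Protocol*

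**What the plan says.** The safety endpoints in Section 1.3 open with a count: "Number of Adverse events and serious adverse events will be monitored during the course of the study". Section 4.2 gives the method of elicitation: "Information about adverse events will be collected by means of a standard question at each visit". The wording is "Have you had any health problems since the previous visit", and no respondent other than the participant is named.

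The inclusion criteria require "An MMSE score between 10 - 24 for the diagnosis of mild to moderate dementia". They also state: "Participants must also be accompanied by a study partner/carer, and this person must be able to assist the participant comply with the study protocol". The partner must be in contact with the participant at least two days per week.

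On timing, the Treatment Protocol in Section 3.3 says that "assessments will be conducted at weeks 2 (via phone), 4, 13, 26, 39, 52 and 65 (follow-up) weeks after the commencement of treatment".

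The partner's one stated part in written self-report is under Drug Accountability, where compliance is measured by "asking participants and their study partner/carer to complete a diary between visits". An adverse event diary is mentioned only in the Treatment Protocol, which has participants keep it on after week 65, and in Appendix 4, item 4.1. Appendix 4, items 2.4 and 3.3, has numbered visit diaries sent out with study medication.

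**The concern.** An open question about the preceding weeks depends on the memory of the person asked. Here that person has mild to moderate dementia, and the interval is usually a quarter of a year. Section 4.2 lists the mild events it expects, among them nausea, headache, dizziness, dry mouth and insomnia. These are the kind that are forgotten and that leave no laboratory trace.

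The event count is a named safety endpoint, good tolerability is part of the hypothesis in Section 1.2, and the three-monthly safety tallies in Section 5.2 use the same reports. Whatever is not elicited is missing from both the ongoing review and the final tolerability statement. A second informant is already required to be present, so the weakness lies in the stated method and is avoidable.

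**Working it through.** **Recall interval.** Contacts fall at weeks 0, 2, 4, 13, 26, 39, 52 and 65. Successive differences are 2, 2, 9, 13, 13, 13 and 13 weeks. With the ±7-day windows of Table 1 the longest interval is 13 + 1 + 1 = 15 weeks. With the ±28-day window of Appendix 4, item 5.2, it is 13 + 4 + 4 = 21 weeks.

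**Channels, and whom each relies on.**
- Visit question (4.2): worded to the participant; relies on recall.
- Week 2 telephone contact: covers the first fortnight only; the informant is not stated.
- Contact between visits (4.2): left to the participant's initiative.
- Laboratory tests: independent of recall, but blind to symptoms.
- Concomitant-medication and procedure checks, weeks 4 to 52: can reveal events that were treated, not those that were not.
- Adverse event diary: described as kept by participants. No text has it reviewed at visits or feeding the event count, and the source records listed in the Data Management Protocol do not name it.
- Between-visit diary (Drug Accountability): completed by participant and partner, with compliance as its stated purpose.

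For an untreated symptom, no channel is stated to draw on the partner's account.

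**What can be said about size.** The protocol states no event rate, no capture rate and no powered comparison of adverse events, so there is no figure to reproduce. The following is an illustration on assumed values only. Let p0 and p1 be the true proportions with an event on placebo and SLT, and c0 and c1 the fractions captured. The observed difference is c1·p1 − c0·p0 and the observed ratio is (c1/c0)·(p1/p0). Assume p0 = 20% and p1 = 35%, so the true difference is 15 points and the true ratio is 1.75. Take n = 238/2 = 119 per arm and two-sided 5%.

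With p0 and p1 now the observed proportions, d their difference, p̄ their mean and q = 1 − p, power is Φ[(d − 1.96·√(2p̄q̄/n)) / √((p1q1 + p0q0)/n)].

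| Capture, SLT / placebo | Observed, SLT v placebo | Difference | Ratio | Power |
|---|---|---|---|---|
| 100% / 100% | 35% v 20% | 15 points | 1.75 | 0.74 |
| 80% / 80% | 28% v 16% | 12 points | 1.75 | 0.61 |
| 50% / 50% | 17.5% v 10% | 7.5 points | 1.75 | 0.39 |
| 80% / 60% | 28% v 12% | 16 points | 2.33 | – |
| 60% / 80% | 21% v 16% | 5 points | 1.31 | – |

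Equal capture shrinks the difference and leaves the ratio alone. Unequal capture moves both, in either direction. The model treats each affected participant as having one event. Someone with several events still counts if any one is captured, so it overstates the loss for such participants. It also works with proportions, whereas the endpoint is a number of events.

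**The case against.** The strongest reply is that the visit question is only one of several sources, so a reader who infers that adverse events rest on it alone goes beyond the text. That is correct: Section 4.2 itself goes on to laboratory tests and participant-initiated contact, and the visit schedule adds the rest.

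The diary argument is also serious. Participants are to continue the adverse event diary after week 65, so one was presumably kept during treatment. Appendix 4, item 4.1, appears to call the same post-trial item both an adverse event diary and a visit diary. A single diary to which the partner contributes is a natural reading, and if it is right, a written record between visits eases the recall problem considerably. It remains an inference, because the protocol neither equates the two diaries nor says that entries are reviewed for adverse events.

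A reader might likewise infer that the partner is not asked. The documents do not say so; they are silent. The partner attends, and sites may well ask. But a practice left unstated can differ between centres.

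It may also be said that the choice of respondent belongs in a site manual. That would carry weight had the protocol left the method open. It prints the question, worded to one person.

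**Conclusion.** The point holds as a risk: the stated method may miss symptomatic, non-laboratory events because it does not direct the question to the available informant or make the diary a source. This rests on the wording of Section 4.2, the MMSE criterion, the 13-week nominal interval and the absence of any text giving the partner a part in adverse event reporting.

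Two stronger readings are not supported. One is that events will be under-counted by some known amount; the documents contain nothing from which to estimate it, and the power figures above describe assumed rates only. The other is that a true excess on SLT will be hidden. Equal forgetting would work that way, but if SLT improved cognition, and with it reporting, an excess could be exaggerated. No net direction is established.

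The primary efficacy analysis is unaffected. The change is worth making because the tolerability conclusion depends on these reports and the remedy is nearly free.

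**What to change.** In Section 4.2:
- put the same standard question to both the participant and the study partner at every adverse event contact during the trial, including the week 2 call;
- state that either person may make adverse event entries in the between-visit diary, and that the diary is reviewed at each visit as an adverse event source;
- record the informant for each report in the eCRF.

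Drug Accountability and the Treatment Protocol should then say whether the compliance diary and the adverse event diary are one document.

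Week 65 must be reconciled at the same time, so that it is clear which contacts are covered. Table 1 and the week 65 visit list show no adverse event recording, while the Treatment Protocol speaks of monitoring and reporting events at follow-up and Appendix 4, item 4.0, lists a safety assessment there.

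The cost is a few sentences, one eCRF field and about a minute per visit, with no added visit. A few more minor events will be recorded in both arms.
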